### Primary outcome measures

2.8

#### Feasibility and acceptability

2.8.1

We will assess feasibility via a retention rate. Rates ≥ 70% from pre- to post-assessment will be considered successful (39, 40). Another indicator will be the number of adverse events reported by the parents or child. Parents/guardians will be asked to report potential adverse events at the end of each session based on the recommendation for internet-intervention (41). Based on previous feasibility studies in children with ARFID we will consider a recruitment rate of ≥1 patient per month as feasible (11, 15). Additionally, based on similar research studies we will apply the following benchmarks enrolment (≥75% eligible participants enrol in the intervention). As an indicator of participants engagement, we will assess the number of times patients tasted new foods over the course of the intervention and how many different foods they tasted per week. Furthermore, we will report the average time needed to complete the intervention.

Additionally, we will ask parents and children at mid- and post treatment to rate the perceived feasibility of different intervention parts (e.g., weekly psychoeducational materials, video therapy sessions). These include ratings on the feasibility of time and effort needed for the intervention, understanding of the materials and satiation with technical quality of the platform on a 6-Point Likert scale (0 = completely agree to 1 = completely disagree). We will also measure parents’ acceptability of the intervention will by the Credibility/Expectancy Questionnaire (CEQ) (42) completed by parents and a single-item for the children.

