Therefore, the aim of the present pilot intervention study will be to evaluate the feasibility and proof-of-concept of a CBT-AR based digital intervention “ExpeditionFood” for children and their parents/caregiver(s). Since sensory sensitivity is the most prevalent presentation of ARFID (4–6), the digital intervention will focus on individuals with sensory sensitivity. Based on the reported high prevalence in children ages 8–14 years (3, 4), the study will include children in this age range. Consequently, this study will simultaneously evaluate the feasibility of CBT-AR for a slightly younger age than in previous CBT AR trials (aged >10 years). Additionally, none of the previous cited interventions have been evaluated in German speaking countries where ARFID prevalence has been established (4, 20, 21). Hence, the primary aim of this study is to assess feasibility in German speaking countries and identify effect sizes for future randomized control trial. We hypothesize that a digital family supported intervention for children with ARFID will be feasible with acceptable recruitment and dropout rates and accepted by children and caregivers. Additionally, we hypothesize that the digital intervention will reduce ARFID symptoms, food neophobia and psychosocial impairment from pre- to post-intervention and will also increase quality of life. Finally, we will investigate if these effects are maintained until the four-week follow-up.

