### Recruitment and sample size

2.3

Recruitment will take place in Germany, Switzerland, Austria where German is (at least one of) the officially spoken languages. We will recruit families via the study’s website, social media (e.g., Instagram, Facebook), flyers, articles in our university press, and advertisements provided to outpatient health care providers affiliated with Konstanz University.

We conducted a power analysis with G*Power (version 3.1) to estimate a sample size, and also considered the sample sizes used in previous one-arm CBT-AR trials (10, 11, 15, 34). Hence, we based our power analysis on a = 0.05 and 1-b = 0.95, and a medium-sized effect size of f = 0.6, which resulted in a sample size of n = 32. To account for an expected dropout rate of 20-30% (15), we will aim to recruit *N* = 40. However, as the primary aim is to assess overall feasibility and acceptability and our main secondary aim is to identify effect sizes for randomized control trials, we are aware that depending on dropout rates the power might not be sufficient to make conclusions about the efficacy.

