### Assessment and data management

2.7

We will assess at screening (t0), baseline (t1), mid-intervention after completion of session 6(t2), post-intervention after completion of session 12(t3) and 4-week follow-up (t4). We will use German translations of all questionnaires. Additionally, parents/guardians will complete brief weekly measures after every session. Self-report data will be assessed via Qualtrics (i.e., for outcome measures, Qualtrics, 2025) and participants will be asked to provide only their assigned participant code when answering the questions. Only the internal study team will have access to the key file in digital password protected folder to link the participants code to the names. Additionally, the secure health platform Curafida (ZTM Bad Kissingen GmbH, 2025) will integrate the software MyMedax for content and reflection questions in self-guided sessions. We will use the secure video call software webPRAX for video call sessions (Healthy Projects GmbH, n.d.). We created a data protection policy and a register of all processing activities with the legal office of Konstanz University for this study. Moreover, a data protection and confidentiality agreement will be in place between the company of the health platform ZTM Bad Kissingen GmbH and the University of Konstanz.

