#### Additional measures

2.9.2

Parents and Children will complete demographic characteristics assessment (e.g., gender, age, ethnicity) and psychiatric/medical history. Furthermore, we will assess comorbid diagnosis by both diagnostic interviews and the self-report measures assessing depression (Children’s Depression Screeners (46)) and anxiety levels (State–Trait Anxiety Inventory (STAI) (47)). Furthermore, we will record video therapy sessions to check for adherence of the study therapist to the intervention. See **Table 2** for a detailed overview including other variables of interest that are not part of the main analysis.

**Table 2 T2:** Overview over measures and measuring points.

Instrument	Author (German-language version)	Construct	Number total items	Subscales	Scale	Caregiver					Children				
						Measuring points					Measuring points				
						0	1	2	3	4	0	1	2	3	4
Primary outcomes (Feasibility)															
Credibility/expectancy Questionnaire	(42)	Treatment expectancy and credibility	6	Expectancy; Credibility	9-point Likert scale from 1 = not at all to 9 = very; 11-point Likert scale from 0 to 100%		x	x	x						
Credibility/Expectancy	Adopted from (48)	Treatment expectancy	1	How sure are you that participating in ExpeditionFood will help you with your eating problems?	9-point Likert scale from 1 = not at all to 9 = very;							x	x	x	
Client satisfaction questionnaire, adapted for inpatient fields of work	(49)	Satisfaction with treatment service	8	/	4-point Likert scale; different scales (e.g., 1 = “excellent” to 4 “bad”			x	x				x	x	
Adverse Events	Adopted from (41)	Adverse events related to the intervention	3		1 Yes/no item; 1 open item to describe the event; 2 severity items on a 4-Point Likert scale 1= not at all to 4= very much		x	x	x	x		x	x	x	x
Secondary outcomes (Measures of ARFID)															
Eating Disorder Examination (EDE) ARFID module	(33)	DSM-5 based diagnosis of ARFID		Includes items on sensory sensitivity and psychosocial impairment	Expert-Rating: Criterion Present Yes/No, symptom severity 0-6		x		x			x		x	
Nine Item Avoidant/Restrictive Food Intake disorder screen (NIAS)	(35, 43) Translated with permission.	Symptom of ARFID	9	picky eating, appetite, fear	6-Point Likert scale 0 = Strongly Disagree to 5 = Strongly Agree.	x	x	x	x	x		x	x	x	x
Food Neophobia Scale (FNS) (shortened version)	(44, 45)	Food Neophobia	7		7-point Likert scale ranging from 1= “strongly disagree” to 7 =“strongly agree.”	x	x	x	x	x		x	x	x	x

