### Proposed statistical analysis

2.10

As our primary aim is to assess feasibility, we will report recruitment rates and retention rates and number of adverse events until post-assessment with descriptive statistics. We will also report feasibility ratings of parents regarding the duration of sessions and materials, number of foods tasted per week, as well as the overall therapy duration of individuals completing the intervention. Acceptability will be descriptively reported based on parents rating on the treatment credibility (Credibility/Expectancy Questionnaire (CEQ) (48) and treatment satisfaction (Client Satisfaction Questionnaire (CSQ) (49)), as well as single-items for children.

As a secondary aim we will analyze ARFID symptoms reduction with paired sample t-test for expert-rated psychosocial impairment and sensory sensitivity (based on the Eating Disorder Examination (EDE) ARFID module, as well as self-report measures of symptoms of ARFID (i.e., Nine Item Avoidant/Restrictive Food Intake disorder screen (NIAS) (43) and Food Neophobic Scale (FNS) (44)) and children’s quality of life will be conducted from pre- to post assessments and pre-to follow-up.

Exploratory, in line with previous research we will also analyze anxiety (STAI (47)) and depression levels (Children’s Depression Screeners (46)) using dependent t-tests to test for potential changes in comorbid symptoms (12, 15).

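### Satisfaction and perceived-feasibility ratings are triggered only by completing sessions 6 and 12, so families who stop early give no rating, or only a mid-treatment one, of the treatment they received

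*Protocol article*

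**What the plan says.** The Introduction of the protocol article hypothesises that the intervention "will be feasible with acceptable recruitment and dropout rates and accepted by children and caregivers". Acceptance is thus part of the primary question, alongside recruitment and dropout.

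The measures and their timing are as follows.

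- **Perceived feasibility** (time, effort, understanding of materials, technical quality). Section 2.8.1: "we will ask parents and children at mid- and post treatment to rate the perceived feasibility of different intervention parts".
- **Satisfaction (CSQ).** Table 2 lists it under the primary outcomes and marks t2 and t3 only, for caregivers and for children.
- **Credibility/expectancy.** Section 2.8.1 names the "Credibility/Expectancy Questionnaire (CEQ) (42) completed by parents and a single-item for the children". Table 2 marks both at t1, t2 and t3. The child item asks "How sure are you that participating in ExpeditionFood will help you with your eating problems".
- **Weekly measures.** The note to Table 2 lists the NIAS, the FNS and the adverse event scale, and no acceptability item.

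Section 2.7 fixes the time points by session completed and not by calendar date: "mid-intervention after completion of session 6(t2), post-intervention after completion of session 12(t3").

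Section 2.10 begins its account of this outcome with "Acceptability will be descriptively reported based on parents rating on the treatment credibility", and adds the CSQ and single items for children. It gives no denominator. Section 2.3 plans for attrition: "To account for an expected dropout rate of 20-30" per cent, with N = 40.

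**The concern.** For this outcome, dropping out may be related to what is being measured. A family that finds the programme too demanding may stop for that reason, and stopping removes its rating. Table 1 places tasting sessions in sessions 3 and 5, so a family can meet food exposure, find it unworkable and leave before the first rating falls due. The article itself anticipates low treatment motivation in children (section 2.1) and family burden (section 2.6).

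Ratings summarised among those who reached the time point describe acceptability to families who stayed. The hypothesis is about the families who start. The two can differ, and the leavers' views are the ones most useful for revising the programme before a randomised trial. A later analysis plan can change a denominator, but it cannot recover ratings that were never requested.

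**Working it through.** **1. The plan's own figures.** Section 2.3 gives n = 32 for alpha 0.05, power 0.95 and effect 0.6. A one-sided paired t-test with a standardised difference of 0.6 needs n = 32 (power 0.953), so the figure reproduces. A two-sided test would need 39. Allowing for dropout, 32 / (1 − 0.20) = 40, which matches N = 40; at 30% it would be 32 / 0.70 = 45.7, so 46. The present point uses only N = 40 and the 20-30% dropout.

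**2. Who rates what**, from sections 2.7 and 2.8.1 and Table 2:

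| Family stops | CEQ / child item | CSQ and perceived feasibility |
|---|---|---|
| before completing session 6 | t1 only (before treatment) | none |
| after session 6, before completing session 12 | t1, t2 | t2 only |
| completes session 12 | t1, t2, t3 | t2, t3 |

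**3. Number without a post-treatment rating.** Raters at t3 = 40 × (1 − d).

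- d = 0.20: 32 raters, 8 missing.
- d = 0.30: 28 raters, 12 missing.

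The article gives no timing of dropout. If half of the leavers go before session 6 (assumption), 4 to 6 families never rate the treatment, and 36 to 34 rate at t2.

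**4. Effect on a favourable share.** Let p_s be the favourable share among raters and p_l the share among leavers had they been asked.

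All-family share = (1 − d) × p_s + d × p_l

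Excess of the raters-only share = d × (p_s − p_l)

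With p_s = 0.90 (assumption; the article defines no cut-off for favourable):

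| p_l (assumption) | d = 0.20: all-family share, excess | d = 0.30: all-family share, excess |
|---|---|---|
| 0.90 (like stayers) | 90%, 0 points | 90%, 0 points |
| 0.50 | 82%, 8 points | 78%, 12 points |
| 0 | 72%, 18 points | 63%, 27 points |

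With p_s = 0.80, the excess is 6 to 9 points at p_l = 0.50 and 16 to 24 points at p_l = 0.

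**5. Effect on a mean score.** Excess = d × gap between raters and leavers. For gaps of 0.5 and 1 SD (assumption), it is 0.10 and 0.20 SD at d = 0.20, and 0.15 and 0.30 SD at d = 0.30.

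**The case against.** Several counter-arguments have force.

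- **Not every acceptability measure has this gap.** A reader might infer that all acceptability ratings come from families who reach session 6 or 12. The article does not support that: the CEQ and the child item are also taken at t1. This stands, and the point is confined to the CSQ and the perceived-feasibility items. The t1 scores record what families expect before treatment, so they do not replace a rating of treatment received.
- **Later leavers are not silent.** Families who leave after session 6 have a t2 rating. This stands. Only those who leave earlier have no rating at all.
- **Dropout is already visible.** Retention is a primary indicator with a 70% benchmark, and acceptability has no threshold that selective non-response could help it pass. Parents can also report difficulties in self-guided sessions from session 2, and adverse events are asked at each session. This lessens the problem. It does not show how leavers judged the treatment, and the reflection prompts are not listed as an outcome.
- **A raters-only analysis is not stated.** Section 2.10 restricts therapy duration to completers and puts no such limit on acceptability, and denominators and withdrawal procedures may sit in a fuller document. For the denominator this is fair. The collection schedule, however, is fixed in this text.
- **The shift is modest against sampling error.** The 95% confidence half-width for a mean of 28-32 raters is about 0.36-0.39 SD, wider than the 0.10-0.30 SD in the working. True, but a confidence interval computed from raters does not reflect selective non-response.
- **Counting non-raters as dissatisfied brings its own bias.** It needs a cut-off that the article lacks, treats families who leave for unrelated reasons as dissatisfied, and counts dropout twice. This stands.

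**Conclusion.** The gap is real, limited in scope and cheap to narrow. The CSQ and perceived-feasibility ratings, both primary feasibility or acceptability measures, are scheduled only at time points that depend on completing sessions 6 and 12. On the plan's own dropout, 8 to 12 of 40 families will lack a post-treatment rating, and those who stop before session 6 will have none.

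A reader might go further and conclude that acceptability is overstated, by as much as 27 points. The article does not establish this. It gives neither reasons for dropout nor its timing. Overstatement is the likely direction, but it requires that leavers would rate lower than stayers. With 90% of raters favourable, the excess runs from 0 to 27 points; 18-27 is its upper end and requires that no leaver would have rated favourably. Nor does the result necessarily omit up to 30% of families altogether: that would need every leaver to go before session 6.

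**What to change.** **Sections 2.7 and 2.8.1.** When a family stops, at whatever session, send the existing CSQ and perceived-feasibility forms to parent and child, with one added item on the reason for stopping.

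**Section 2.10.** Report the number of raters and non-raters out of all families who started. Show the last available rating of leavers (t2 or exit, labelled as such) beside the post-treatment raters-only result. If non-raters are ever scored as not favourable, define favourable beforehand and present that figure only as a labelled worst-case bound.

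**Cost.** One extra online trigger for about 8 to 12 families, using forms already built apart from the reason item, plus a few lines of reporting text. Some stopping families will not reply, so the gap shrinks without closing, and the acceptability figure may come out less favourable.

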### Secondary outcomes

2.9

#### Clinical outcomes

2.9.1

As proof of concept, we will assess ARFID symptoms. We will therefore administer the Nine Item Avoidant/Restrictive Food Intake disorder screen (NIAS (35, 43)) and a shortened version of the Food Neophobia Scale (FNS (44, 45)) at each time point. Additionally, we will use the parent- and child- version of the ARFID module of the ChEDE (33) to assess the fulfilment of ARFID criteria and to assess ARFID presentation. The subscales psychosocial impairments and sensory sensitivity will be used as an indicator for reduction in ARFID symptoms according to expert-ratings. Additionally, we will examine exploratory the subscales ChEDE lack of interest and fear of negative consequences to examine if changes in sensory sensitivity also affect the other presentation (19). Furthermore, the number of integrated foods will be reported as a treatment outcome based on parents’ report.

#### Additional measures

2.9.2

Parents and Children will complete demographic characteristics assessment (e.g., gender, age, ethnicity) and psychiatric/medical history. Furthermore, we will assess comorbid diagnosis by both diagnostic interviews and the self-report measures assessing depression (Children’s Depression Screeners (46)) and anxiety levels (State–Trait Anxiety Inventory (STAI) (47)). Furthermore, we will record video therapy sessions to check for adherence of the study therapist to the intervention. See **Table 2** for a detailed overview including other variables of interest that are not part of the main analysis.

**Table 2 T2:** Overview over measures and measuring points.

Instrument	Author (German-language version)	Construct	Number total items	Subscales	Scale	Caregiver					Children				
						Measuring points					Measuring points				
						0	1	2	3	4	0	1	2	3	4
Primary outcomes (Feasibility)															
Credibility/expectancy Questionnaire	(42)	Treatment expectancy and credibility	6	Expectancy; Credibility	9-point Likert scale from 1 = not at all to 9 = very; 11-point Likert scale from 0 to 100%		x	x	x						
Credibility/Expectancy	Adopted from (48)	Treatment expectancy	1	How sure are you that participating in ExpeditionFood will help you with your eating problems?	9-point Likert scale from 1 = not at all to 9 = very;							x	x	x	
Client satisfaction questionnaire, adapted for inpatient fields of work	(49)	Satisfaction with treatment service	8	/	4-point Likert scale; different scales (e.g., 1 = “excellent” to 4 “bad”			x	x				x	x	
Adverse Events	Adopted from (41)	Adverse events related to the intervention	3		1 Yes/no item; 1 open item to describe the event; 2 severity items on a 4-Point Likert scale 1= not at all to 4= very much		x	x	x	x		x	x	x	x
Secondary outcomes (Measures of ARFID)															
Eating Disorder Examination (EDE) ARFID module	(33)	DSM-5 based diagnosis of ARFID		Includes items on sensory sensitivity and psychosocial impairment	Expert-Rating: Criterion Present Yes/No, symptom severity 0-6		x		x			x		x	
Nine Item Avoidant/Restrictive Food Intake disorder screen (NIAS)	(35, 43) Translated with permission.	Symptom of ARFID	9	picky eating, appetite, fear	6-Point Likert scale 0 = Strongly Disagree to 5 = Strongly Agree.	x	x	x	x	x		x	x	x	x
Food Neophobia Scale (FNS) (shortened version)	(44, 45)	Food Neophobia	7		7-point Likert scale ranging from 1= “strongly disagree” to 7 =“strongly agree.”	x	x	x	x	x		x	x	x	x
Diagnostic Interview for Mental Disorders in Children and Adolescents	(36)	Diagnosis of comorbid symptoms (DSM-5)			Criterion fulfilled yes/partially/no		x								
Children’s Depression Screeners (ChilD-S)	(46)	Depression	8		4 Point Likert scale; 0 = “agree” to 3 = “disagree”							x	x	x	x
State–Trait Anxiety Inventory—Child version trait subscale	(47)	Trait Anxiety	20		3-response scale							x	x	x	x
Generic Quality of Life Instrument for Children-Revised-	(51)	Health-related quality of life	24	Physical well-being psychological wellbeing, self-esteem, family, friends, education/school	5-point Likert scale from 0 = “never” to 4 = “always”							x	x	x	x
Working alliance inventory—short revised	(52, 53)	Therapeutic alliance	12		5-point Likert scale from 1 = “rarely” to 5 “always”			x	x	x					
Therapeutic Alliance Scales for Children	(54)	Therapeutic alliance	12	Bond/working alliance; Positive and negative aspects of the emotional bond	4-Point Likert scale from 1 = “not at all” to 4 = exactly right”								x	x	x
Additional measures															
Children Eating Disorder Examination-Questionnaire (EDE-Q8)	(55, 56)	eating disorder psychopathology	8	restraint, eating concern, weight concern, and shape concern	0–6 scale = number of days in the previous 28; or (b) “Not at all” to “Markedly, ratio scale	x						x	x	x	x
Children Eating Disorder Examination-Questionnaire Parent version (EDE-QP-parent version)	(56)	eating disorder psychopathology	28	restraint, eating concern, weight concern, and shape concern	0–6 scale = number of days in the previous 28; or (b) “Not at all” to “Markedly, ratio scale	x									
The Affinity for Technology Interaction (ATI) Scale	(57)	Affinity for Technology Interaction	9		6-point Likert scale, 1 = “strongly disagree” to 6 = “strongly agree”		x								

ARFID, avoidant/restrictive food intake disorder. Assessment will take place at screening (t0), baseline (t1), mid-intervention (t2), post-intervention (t3) and 4-week follow-up (t4). Additionally, parents will be asked to fill out weekly the FNS; NIAS, and adverse event scale. Furthermore, number of integrated new foods will be tracked by caregivers from week 3 onwards. Demographic characteristics (e.g., gender, age) will be assessed at screening and baseline and parent-child interaction regarding food at pre-, mid and post-treatment.

### Proposed statistical analysis

2.10

As our primary aim is to assess feasibility, we will report recruitment rates and retention rates and number of adverse events until post-assessment with descriptive statistics. We will also report feasibility ratings of parents regarding the duration of sessions and materials, number of foods tasted per week, as well as the overall therapy duration of individuals completing the intervention. Acceptability will be descriptively reported based on parents rating on the treatment credibility (Credibility/Expectancy Questionnaire (CEQ) (48) and treatment satisfaction (Client Satisfaction Questionnaire (CSQ) (49)), as well as single-items for children.

As a secondary aim we will analyze ARFID symptoms reduction with paired sample t-test for expert-rated psychosocial impairment and sensory sensitivity (based on the Eating Disorder Examination (EDE) ARFID module, as well as self-report measures of symptoms of ARFID (i.e., Nine Item Avoidant/Restrictive Food Intake disorder screen (NIAS) (43) and Food Neophobic Scale (FNS) (44)) and children’s quality of life will be conducted from pre- to post assessments and pre-to follow-up.

Exploratory, in line with previous research we will also analyze anxiety (STAI (47)) and depression levels (Children’s Depression Screeners (46)) using dependent t-tests to test for potential changes in comorbid symptoms (12, 15).

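### Adverse events are reported only to post-assessment although they are collected at the 4-week follow-up, and the reporting window has no stated start

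*Protocol article*

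**What the plan says.** Four places in the protocol article bear on this.

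- **Section 2.10 (Proposed statistical analysis)** sets the report for the primary feasibility outcomes: "recruitment rates and retention rates and number of adverse events until post-assessment with descriptive statistics". It names an end point and no start. The next paragraph plans paired t-tests of expert-rated and self-reported ARFID symptoms, food neophobia and quality of life, both from baseline to post-treatment and from baseline to follow-up.
- **Table 2** lists adverse events among the primary (feasibility) outcomes, with the construct "Adverse events related to the intervention". The scale is marked at t1, t2, t3 and t4 for caregivers and again for children. The table note defines t1 as baseline and t4 as the 4-week follow-up.
- **Section 2.8.1 (Feasibility and acceptability)** makes the number of events reported by parents or child a feasibility indicator. It adds that parents are "asked to report potential adverse events at the end of each session".
- **Section 2.7 (Assessment and data management)** says that "parents/guardians will complete brief weekly measures after every session". The note to Table 2 says "parents will be asked to fill out weekly the FNS; NIAS, and adverse event scale".

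**The concern.** The article itself fixes the reporting window for harm, and that window stops before the last scheduled collection of harm data. This is not a detail left to a later document. Followed literally, the sentence in section 2.10 leaves the t4 adverse event answers out of the report on a primary feasibility indicator, while the same section carries the secondary outcomes through to t4.

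The imbalance matters in a single-arm paediatric pilot whose findings are meant to inform a randomised trial. A reader would see whether gains last to follow-up, but not whether problems appeared or continued in the weeks after the final session.

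The start of the window is a lesser matter. The scale is given at t1, before any intervention, so a count with an end and no beginning leaves unclear what becomes of those answers. Two analysts following the same sentence could produce different totals.

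**Working it through.** The plan states no adverse event rate, count or benchmark, so there is no figure to reproduce. The check compares text with table and then sizes the gap.

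**Collection against reporting**

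| Measuring point | Scale scheduled (Table 2) | Adverse event report (section 2.10) | Secondary outcomes (section 2.10) |
|---|---|---|---|
| t1, baseline | caregiver and child | not stated | used as the starting value |
| t2, mid-intervention | caregiver and child | inside the window | not in the named tests |
| t3, post-intervention | caregiver and child | end of the window | tested against baseline |
| t4, 4-week follow-up | caregiver and child | outside the window | tested against baseline |

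The t4 row holds the mismatch. The t1 row holds the undefined start.

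**Size of the omitted period**

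Inputs: a 12-week programme at the recommended pace of one session per week (section 2.6), and a follow-up 4 weeks later (section 2.7).

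- Nominal observation after the start of treatment: 12 + 4 = 16 weeks.
- Reported: 12 weeks. Omitted: 4 weeks.
- Share omitted: 4 / 16 = 25% of nominal calendar time.

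The weekly pace is only recommended, so the true share varies by family. A family that takes longer over the sessions has a smaller share omitted.

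**The same gap counted in reporting occasions**

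- Caregivers: 12 end-of-session reports plus t2, t3 and t4 give 15 occasions after the start of treatment. t4 is 1 / 15, about 7%.
- Children: the reports between measuring points are requested from parents only, so children have t2, t3 and t4. t4 is 1 / 3, about 33%.

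The size therefore depends on the measure: 25% of nominal time, about 7% of caregiver occasions, and one of three child readings after baseline. None of these is a share of events, for which the plan gives no rate.

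**The baseline reading**

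Its possible effect on the count cannot be computed. The article gives no background event rate and does not say whether the t1 answers enter the total.

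**The case against.** The best defence is that the sentence describes the primary feasibility outcomes, and retention is itself defined from pre- to post-assessment in section 2.8.1. On that reading, the adverse event window simply matches the primary window, and t4 events could still be described separately. This stands in part: the article does not say that t4 answers will go unreported. But it does state a rule for adverse events, and that rule ends at t3. Nothing else in the article says where the t4 answers will appear.

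A reader might also infer four stronger claims. The document does not support them.

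- **That the count is wrong at both ends.** Nothing says that t1 answers are counted. They may serve as a background reading, or the mark in Table 2 may be a slip. The start is undefined; no miscount is shown. At the late end, the count would be correct for its declared window, but incomplete against what is collected.
- **That per-session and weekly collection contradict each other.** Section 2.7 uses the two terms for one schedule. The wording is loose, but it does not set two rules.
- **That harms leading to dropout go uncounted.** Routine reports do follow session completion, and t3 follows session 12, so reports from families who stop could be missed. But the article does not say that such families are not asked, and contact at withdrawal may well be set out in the full protocol. At the planned 20–30% dropout, 40 × 0.20 = 8 to 40 × 0.30 = 12 families would leave. That is dropout for any reason and does not measure missed harms.
- **That a quarter of the safety data is lost.** The 25% is calendar time only, as the occasion counts show.

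Calendar-weekly collection for everyone and event rates per child-week would be design or presentation preferences. They do not correct anything the article states wrongly.

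**Conclusion.** The point holds in limited form and is a free improvement. Section 2.10 and Table 2 do not agree on how far adverse events are followed. As written, harm is reported to t3 and benefit to t4, which leaves out the last 4 of 16 nominal weeks and one of the three child readings after baseline. Separately, the window has no stated start although the scale is given before treatment.

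The conclusion about t4 rests on reading the post-assessment limit as applying to adverse events, the item it directly follows. The 25% assumes the recommended pace of one session per week. No claim is made about how many events would be missed or wrongly included, because the article gives no rate from which to estimate either.

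**What to change.** Change the sentence in section 2.10 so that it:

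1. reports adverse events from the first session through t4, for all enrolled families;
2. shows the t1 answers separately as background and does not add them to the count;
3. gives the number of children with at least one event alongside the total number of events.

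Recruitment and retention can keep their present definitions. If the authors want an adverse event figure for the treatment period alone, they can give the count to t3 as a subtotal beside the count to t4.

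The cost is reporting wording. The t4 scale is already scheduled for both informants, so no new assessment is needed. The total may be slightly higher than under the present wording.
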